### **Exploratory endpoints**

10. Description of immune histochemical changes and expression of selected cytokines before and after apremilast therapy, assessed in vulvar or vaginal biopsies at week 0 and 24
11. Description of extragenital lichen planus at week 0, 16 and 24
12. Clinical photos taken at week 0 and week 24
13. Adverse events

## **3 OVERALL STUDY DESIGN**

There are very few controlled studies on treatment of GELP in women. The Cochrane Database systematic review on treatment of erosive lichen planus affecting mucosal sites(9) concludes that more RCTs on a larger scale are needed in the oral and genital ELP populations and suggest that future studies should have standardized outcome variables that are clinically important to affected individuals.

This is a phase 2, single-center, randomized, placebo-controlled, double-blind, parallel-group study.

An equal number of participants are randomized to apremilast- or placebo treatment arms. Based on experience from previous studies on apremilast used for other indications, effect is usually achieved within 3-4 months,(29) with some expected additional effect for another two months.

**Screening** will be performed no more than 90 days prior to baseline visit. Patients will receive information on participation at screening visit.

Patients who qualify for participation according to inclusion criteria and who have signed the informed consent form will be included at baseline visit (day 0). They will be randomized at inclusion to receive either study medication (apremilast) or placebo. Screening and baseline visit may be on the same day, but preferably patients will have at least 24 hours between screening and baseline to allow adequate time for patient information/ informed consent.

**Randomization** will be performed in the electronic data capture system Viedoc which includes a randomization module and both patients and clinicians will be blinded for the allocation. The study is double-blinded for the randomization throughout the treatment period and until end of trial.

Following randomization, 21 patients will receive study medication (oral apremilast) and 21 patients will receive oral placebo. Initial standard titration of dose day 1-6 is followed by standard dose of 30 mg apremilast b.i.d. or placebo b.i.d for a total period of 24 weeks. Tablet blister cards are identical in appearance in both groups.

|                            |                                                                                                                                                                                                                                |
|----------------------------|--------------------------------------------------------------------------------------------------------------------------------------------------------------------------------------------------------------------------------|
| Study Period        | First patient enrolled: 24.09.2019                                                                                                                                                                                             |
|                            | Anticipated recruitment period: 01.03.2019 – 01.07.2021                                                                                                                                                                        |
|                            | Estimated date of last patient completed: 31.12.2021                                                                                                                                                                           |
| Treatment Duration: | 24 weeks.
The end of the trial is defined as the date of the last visit of the last patient undergoing the trial.                                                                                                           |
| Follow-up:          | At the end of study at week 24 or if earlier withdrawal from study, patients will be given an appointment with one of the participating clinicians ([name] or [name]) for regular clinical follow-up after approximately 3-6 months. |

[figure not shown]

**Figure 1.**

## 4 STUDY POPULATION

### 4.1 Selection of Study Population

The Vulva Clinic at Oslo University Hospital, Oslo, Norway is a national tertiary referral center for women with chronic vulval diseases. In 2015, more than 700 consultations were carried out, with approximately half of the patients living in the southeast region of Norway.

150-200 patients with genital lichen planus are registered in the clinic database. 4 specialists, 2 gynecologists and 2 dermatologists ([name] and [name]) are employed and collaborate with other health care professionals. Study participants will be recruited mainly from the Vulva Clinic but may also be referred from other specialized vulva services and specialists outside OUH.

#### Number of Patients

42 patients will be included in this trial, 21 subjects in active treatment group and 21 subjects in placebo group.

### 4.2 Inclusion Criteria

All of the following conditions must apply to the prospective patient at screening prior to receiving study medication:

- >18 years of age
- Female
- Moderate to severe GELP with the diagnosis based on characteristic clinical and/or histological features. Minimum GELP score 5/30 in vagina and/or vulva (scored separately), of which erythema and pain  $\geq 1$  are mandatory
- Sexually active patients of childbearing potential must agree to use highly effective contraception during treatment and 28 days after the last dose of IMP
- Signed informed consent and expected cooperation of the patients for the treatment and follow up is obtained and documented according to ICH GCP, and national/local regulations.

A woman is considered of childbearing potential (WOCBP), i.e. fertile, following menarche and until becoming post-menopausal unless permanently sterile. Permanent sterilization methods include hysterectomy, bilateral salpingectomy and bilateral oophorectomy. A postmenopausal state is defined as no menses for 12 months without an alternative medical cause.

Highly effective birth control methods: (36)

- combined (estrogen and progestogen containing) hormonal contraception associated with inhibition of ovulation; oral, intravaginal or transdermal
- progestogen-only hormonal contraception associated with inhibition of ovulation, oral, injectable or implantable
- intrauterine device
- intrauterine hormone-releasing system
- bilateral tubal occlusion

- vasectomized partner, provided that partner is the sole sexual partner of the WOCBP trial participant and that the vasectomized partner has received medical assessment of the surgical success
- sexual abstinence, defined as refraining from heterosexual intercourse during the entire period of risk associated with the study treatments.

### 4.3 Exclusion Criteria

Patients will be excluded from the study if they meet any of the following criteria:

- Patients receiving other systemic immune modulating therapy. Immune modulating therapy other than the study drug is prohibited during the study. Subjects who have been taking the following medications must adhere to the following minimum washout periods:
  - Four weeks prior to the day of inclusion for non-biologic systemic immunosuppressive agents
  - Twelve weeks prior to the day of inclusion for adalimumab, infliximab, etanercept and similar agents
  - Twelve months prior to the day of inclusion for rituximab.
- Concomitant use of strong CYP3A4 enzyme inducers. Apremilast exposure is decreased when administered concomitantly with strong inducers of CYP3A4 and may result in reduced clinical response. The use of strong CYP3A4 enzyme inducers (e.g. rifampicin, phenobarbital, carbamazepine, phenytoin and St. John's Wort) with apremilast is not recommended.(29)
- Inadequate birth control, pregnancy and/or breast-feeding
- Depression and suicidal ideation (GHQ-28 score more than 7/28)
- Patients with severe renal impairment (creatinine clearance of less than 30mL per minute) as described in SmPC
- Patients with active tuberculosis, serious infections or cancer
- Unexplained and clinically significant weight loss in underweight patients
- Hypersensitivity to the active substance or to any of the excipients (listed in SmPC)
- Hereditary problems of galactose intolerance, lactase deficiency or glucose-galactose malabsorption
- Participating in another trial that might affect the current study or there should be minimum 90 days between participation in another intervention trial

## 5 TREATMENT

For this study apremilast and placebo are defined as Investigational Medicinal Products (IMP). Apremilast is approved for use in Norway but for another indication (psoriasis and psoriatic arthritis). Subjects will receive a standard dose of 30 mg BID.

Placebo and active study medication will be manufactured and supplied to the investigators by Celgene Corporation. Import will be performed by The Hospital Pharmacy. Apremilast will be supplied as 10, 20, or 30 mg tablets for oral administration. Additional description of the study drug can be found in the Investigator's Brochure.

After import and registration by the pharmacy, the IMPs will be stored in the pharmacy in a locked, safe area with temperature data logging and access limited to designated study personnel or pharmacists. Apremilast should not be stored above 30°C.

The IMP will be packaged in blister cards and labelled by Celgene and will be administered to the subjects by authorized pharmacy personnel.

There will be sufficient medication in the blister cards to cover up to 1-month delay in the scheduled assessments.

Note: Following Celgene's sale to Amgen of the global rights to Otezla®, rights and obligations under the contract with Celgene is transferred to Amgen from May 1, 2020.

### **5.1 Dosage and Drug Administration**

Apremilast 30 mg and placebo tablets are administered orally, twice daily (morning and evening), approximately 12 hours apart. To reduce risk of gastrointestinal symptoms, dose titration day 1-6 is recommended and apremilast will be administered according to the following schedule:

Day 1: 10 mg in morning

Day 2: 10 mg in morning and 10 mg in evening

Day 3: 10 mg in morning and 20 mg in evening

Day 4: 20 mg in morning and 20 mg in evening

Day 5: 20 mg in morning and 30 mg in evening

Day 6 and thereafter: 30 mg twice daily

This is similar to the standard dosage regimen for psoriasis and psoriatic arthritis.

For details on dosing regime and tablet kits refer to appendix 1, blinded kit template.

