## APPENDIX A -BLINDED KIT TEMPLATE

### Blinded Titration Card – 10-20-30mg

|  |  |    |     |                                                                                   |     |     |  |    |     |                                                                                     |     |     |
|--|--|----|-----|-----------------------------------------------------------------------------------|-----|-----|--|----|-----|-------------------------------------------------------------------------------------|-----|-----|
|  |  | 1  | 10  | [figure not shown] | 20p | 30p |  | 1  | 10p | [figure not shown] | 20p | 30p |
|  |  | 2  | 10  |                                                                                   | 20p | 30p |  | 2  | 10p |                                                                                     | 20p | 30p |
|  |  | 3  | 10  |                                                                                   | 20p | 30p |  | 3  | 10p |                                                                                     | 20  | 30p |
|  |  | 4  | 10p |                                                                                   | 20  | 30p |  | 4  | 10p |                                                                                     | 20  | 30p |
|  |  | 5  | 10p |                                                                                   | 20  | 30p |  | 5  | 10p |                                                                                     | 20p | 30  |
|  |  | 6  |     |                                                                                   |     | 30  |  | 6  |     |                                                                                     |     | 30  |
|  |  | 7  |     |                                                                                   |     | 30  |  | 7  |     |                                                                                     |     | 30  |
|  |  | 8  |     |                                                                                   |     | 30  |  | 8  |     |                                                                                     |     | 30  |
|  |  | 9  |     |                                                                                   |     | 30  |  | 9  |     |                                                                                     |     | 30  |

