## 30mg – Treatment Card (Active)

Note: To support ongoing blinding across titration & treatment patients will need to take 3 tablets a day for the first 5 days with each new card received by the patient.

|  |    |     |                                                                                   |     |    |  |    |     |                                                                                     |     |    |
|--|----|-----|-----------------------------------------------------------------------------------|-----|----|--|----|-----|-------------------------------------------------------------------------------------|-----|----|
|  | 1  | 10p | [figure not shown] | 20p | 30 |  | 1  | 10p | [figure not shown] | 20p | 30 |
|  | 2  | 10p |                                                                                   | 20p | 30 |  | 2  | 10p |                                                                                     | 20p | 30 |
|  | 3  | 10p |                                                                                   | 20p | 30 |  | 3  | 10p |                                                                                     | 20p | 30 |
|  | 4  | 10p |                                                                                   | 20p | 30 |  | 4  | 10p |                                                                                     | 20p | 30 |
|  | 5  | 10p |                                                                                   | 20p | 30 |  | 5  | 10p |                                                                                     | 20p | 30 |
|  | 6  |     |                                                                                   |     | 30 |  | 6  |     |                                                                                     |     | 30 |
|  | 7  |     |                                                                                   |     | 30 |  | 7  |     |                                                                                     |     | 30 |
|  | 8  |     |                                                                                   |     | 30 |  | 8  |     |                                                                                     |     | 30 |

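### Section 5.1 and the blinded kit template disagree on the Day 2 evening dose, and the template's note of three tablets a day does not match the six on each card

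*Protocol*

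**What the plan says.** Section 5.1 of the protocol lists the active dose for each titration day. The entry that matters here is "Day 2: 10 mg in morning and 10 mg in evening". Before it comes a single 10 mg dose on the first morning. After it the daily total climbs to 30, 40 and then 50 mg on the third, fourth and fifth days, each split between two intakes, and the full dose of 30 mg twice daily starts on the sixth. The section then sends the reader to the kit template: "For details on dosing regime and tablet kits refer to appendix 1, blinded kit template". The list of appendices has it as Appendix A. Because of that reference, the template is part of the treatment specification.

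Appendix A shows three layouts: the active titration card ("Blinded Titration Card – 10-20-30mg"), the active 30 mg treatment card and the placebo card. Each has two panels per day. On Days 1 to 5 each panel holds a 10, a 20 and a 30 mg tablet position, with the suffix p read as placebo. From Day 6 each panel holds one tablet. A note on the active treatment card, which gives blinding as its reason, says that "patients will need to take 3 tablets a day for the first 5 days with each new card received by the patient".

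**The concern.** Two parts of the same specification describe what a patient takes in the first days of a card, and they do not agree.

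The first disagreement is a dose. Section 5.1 has an active 10 mg tablet on the evening of Day 2, and the titration card has placebo in all three positions of the second Day 2 panel.

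The second is a count. The note gives three tablets a day, and the layouts hold six.

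What is at stake is a single, consistent statement of the titration and of the daily tablet number. Anyone who makes the kits, explains them to patients or reviews returned blister cards (section 5.6) has to work from one or the other.

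**Working it through.** **Inputs.** The specified doses come from section 5.1. The card contents come from the titration card in Appendix A. The panels carry no morning or evening label in the text available, so left is taken as morning and right as evening. Active dose per panel is the sum of the tablets without the suffix p.

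**Dose comparison (active mg, morning + evening).**

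| Day | Section 5.1 | Card, left panel | Card, right panel | Card total | Agree? |
|---|---|---|---|---|---|
| 1 | 10 + 0 = 10 | 10, 20p, 30p | 10p, 20p, 30p | 10 + 0 = 10 | yes |
| 2 | 10 + 10 = 20 | 10, 20p, 30p | 10p, 20p, 30p | 10 + 0 = 10 | **no** |
| 3 | 10 + 20 = 30 | 10, 20p, 30p | 10p, 20, 30p | 10 + 20 = 30 | yes |
| 4 | 20 + 20 = 40 | 10p, 20, 30p | 10p, 20, 30p | 20 + 20 = 40 | yes |
| 5 | 20 + 30 = 50 | 10p, 20, 30p | 10p, 20p, 30 | 20 + 30 = 50 | yes |
| 6 | 30 + 30 = 60 | 30 | 30 | 30 + 30 = 60 | yes |

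Totals over Days 1 to 5:

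- Section 5.1: 10 + 20 + 30 + 40 + 50 = 150 mg
- Card: 10 + 10 + 30 + 40 + 50 = 140 mg
- Difference: 150 − 140 = 10 mg, which is the one Day 2 evening tablet

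**Size against the whole course.** Planned exposure over 24 weeks (168 days) by section 5.1 is 150 mg plus 163 days at 60 mg, or 150 + 9,780 = 9,930 mg. The gap is 10 / 9,930, about 0.1%.

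**Tablet count, Days 1 to 5.** Each of the three layouts holds 3 tablets × 2 panels = 6 a day, and section 5.1 requires dosing morning and evening. The note says 3 a day. From Day 6 the cards hold 1 × 2 = 2 a day, and the note does not cover those days. If the note means three per intake, then 3 × 2 = 6 and the count agrees with the cards.

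**The case against.** The Day 2 point rests on one letter in one cell of a table read from PDF, with a figure missing inside each panel and no panel labels. This caution stands, and it is why the original must be checked first. A general reading fault is unlikely, because the same panel assignment reproduces Days 1, 3, 4, 5 and 6 exactly.

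The note is the weaker half. It sits in a kit template, explains the blinding and is written about patients rather than to them. With three tablets per panel and twice-daily dosing, three per intake is a natural reading. That is a fair account of what was probably meant, but the wording is per day and still needs correcting.

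A reader might go further and infer any of the following. The protocol does not support them:

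- **Patients received a dose other than the one specified.** Appendix A is a design, not a manufacturing or dispensing record.
- **Patients would take half a card by following the note.** Nothing shows that patients are given this sentence. Section 5.7 puts dosing instructions on the label, and section 5.6 has the study team explain which cards to use and in what order.
- **About 17% of treatment days are affected.** That figure (five cards × 5 days + 3 days of a sixth = 28; 28 / 168) assumes each 33-day card is used to its end in sequence. The protocol does not say so, and section 5 says the cards include supply for delayed visits.
- **Compliance scores or per-protocol results would be distorted.** Section 10.3 says only that per-protocol analyses will be done. Sections 5.5 and 5.6 record interruptions and unused tablets but define no tablet-count score.

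**Conclusion.** Two contradictions stand on the face of the protocol. Section 5.1 and the active titration card differ in one cell, the Day 2 evening dose: 20 mg against 10 mg on that day, and 150 mg against 140 mg over Days 1 to 5. The note's three tablets a day differs from the six shown on Days 1 to 5 of all three card layouts, unless it means three per intake.

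The dose finding assumes that the left and right panels are morning and evening, that p denotes placebo, and that the Day 2 cell was read correctly from the PDF. The count finding needs none of these beyond both panels being used each day.

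A one-off difference of 10 mg in the first week, in the active arm only, is unlikely to affect an intention-to-treat comparison at week 24, and no such effect is claimed. This is an inconsistency in the treatment specification that should be corrected.

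**What to change.** 1. Check the Day 2 row of the titration card against the original template and the manufactured card.
2. Reconcile section 5.1, that row of Appendix A and the tablet-count note, so that the text, the card and any instruction given to patients agree. This review does not say which dose or count is right.
3. Have the note state whether its number is per intake or per day.
4. Correct the cross-reference in section 5.1, which calls the appendix 1 where the list of appendices has A.

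The cost is a correction to the text or the template, plus a check of any patient instruction that repeats the note. If the manufactured card already matches section 5.1, the dose part needs only a correction to the template in the protocol.

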### **5.2 Duration of Therapy**

The IMP will be given for 24 weeks.

### **5.3 Schedule Modifications**

Participants will not be able to reduce apremilast (or placebo) dose in the study.

If a subject misses 4 or more consecutive days of dosing, the PI should be contacted for further instruction. The investigator will decide on further treatment with the IMP based on clinical

evaluation, and the dose will be registered in the CRF. Criteria for treatment discontinuation are listed in 6.5.

## **5.4 Concomitant Medication**

**5.4.1.** All systemic medication (incl. vitamins, herbal preparation and other “over-the-counter” drugs) used by the patient will be recorded in the patient’s file and CRF. Prohibited concomitant medications are listed in the exclusion criteria.

Concomitant treatment with other medicinal products that are likely to increase the risk of psychiatric events should be evaluated carefully and preferably be avoided.

**Topical medications:** In the genital area, patients are allowed to use potent topical steroid (clobetasol propionate or similar) as needed during the study. They will record frequency of use per week in the patient's diary. Study subjects are not allowed to use other immunomodulating topical medications in the genital area.

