## Risks/ benefits

Different benefits and risks are associated with the proposed study regime of apremilast in psoriasis and psoriatic arthritis. Known effects of apremilast are summarized in 1.3. Potential benefits in GELP are reduced pain and inflammation, reduced sexual distress and improved quality of life.

According to the SmPC, the most commonly reported adverse reactions in Phase III clinical studies have been gastrointestinal (GI) disorders including diarrhea (15.7%) and nausea (13.9%). These GI adverse reactions were mostly mild to moderate in severity, with 0.3% of diarrhea and 0.3% of nausea reported as being severe. These adverse reactions generally occurred within the first 2 weeks of treatment and usually resolved within 4 weeks. The other most commonly reported adverse reactions included upper respiratory tract infections (8.4%), headache (7.9%), and tension headache (7.2%). Overall, most adverse reactions were considered to be mild or moderate in severity. Patients 65 years of age or older may be at a higher risk of complications.

Of special concern for GELP patients is diarrhea, which may cause additional irritation/ inflammation of the genital area during the first weeks of treatment. Patients will be given advice on hygiene measures and use of topical treatments such as moisturizing and barrier creams at initiation of treatment to reduce this.

Psychiatric adverse effects have been reported with apremilast treatment. The SmPC describes symptoms of depression as common ( $\geq 1/100$  to  $< 1/10$ ). Post-marketing studies and clinical studies have reported uncommon cases of suicidal ideation and behaviour. The exclusion criteria reflects this, and measures to prevent psychiatric side effects are listed in table 1 and described further in Ch. 8.

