### **Baseline visit (week 0):**

Randomization and initiating apremilast or placebo treatment  
Medical history including current use of topical steroid (no of days used per week last 4 weeks).  
Clinical examination  
Weight  
Safety evaluation  
Clinical photo  
PGA, GELP, PtGA, FSDS-R, DLQI, GHQ-28  
Vulval and/ or vaginal biopsy

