### **Clinical status/ examination:**

- Inspection of the genital area, the cavum oris and, if relevant, other affected skin areas
- Blood pressure
- Cardiac and pulmonary auscultation

**Patients' weekly assessment:** All patients will receive a diary at baseline for weekly registration of steroid use (no. of days per week), genital pain assessment (VAS scale 0-10) and adverse events. The diary is collected at week 16 and week 24. Participants may also use ViedocMe weekly for electronic registration.

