- **VAS:** VAS is recorded on a visual linear scale ranging from 0 (no pain) to 10 (worst imaginable pain)
- **PGA score:** 5-point disease severity scoring system, assessed by the clinician

0 - Clear

1 - Almost clear

2 - Mild

3 - Moderate

4 - Severe

- **PtGA:** 5-point disease severity scoring system (as described for PGA), assessed by the patient
- **Topical steroid use:** Frequency of application is recorded in the patient diaries as the number of days being used per week.

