#### **10.5.3 Primary analysis**

The primary outcome, i.e. mean difference in GELP score at 24 weeks between the randomized groups, will be assessed with an ANCOVA model adjusting for the GELP score at baseline. We will use a 5% significance level in statistical analysis. The result will be reported as mean difference between the apremilast and placebo treated patients with a 95% confidence interval and a p-value as estimated from the ANCOVA model.

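### Genital steroid is measured only as days per week, which hides escalation in daily users, and the week-0 steroid days already collected are left out of the primary model

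*Protocol*

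**What the plan says.** Protocol section 5.4 leaves potent genital steroid free in both arms: "In the genital area, patients are allowed to use potent topical steroid (clobetasol propionate or similar) as needed during the study". It adds one restriction: "Study subjects are not allowed to use other immunomodulating topical medications in the genital area". Its rule for recording in the patient file and CRF names systemic medication only.

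Section 7.1 defines the steroid measure: "Frequency of application is recorded in the patient diaries as the number of days being used per week". The patients' weekly assessment in section 6.2 gives the diary the same content: "weekly registration of steroid use (no. of days per week), genital pain assessment (VAS scale 0-10) and adverse events". Weekly steroid use from the diary is a secondary endpoint (section 2.2).

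At the baseline visit, section 6.2 collects topical steroid use as days per week over the preceding 4 weeks. The primary outcome in section 10.5.3 "will be assessed with an ANCOVA model adjusting for the GELP score at baseline"; no other covariate is named. Section 10.2.1 describes permuted blocks with 1:1 allocation and states no stratification factor.

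Section 10.5.6 names topical steroid use as an intercurrent event that may influence the conclusion and leaves its handling to the SAP. Section 1.4 describes both arms as added to common topical therapy.

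**The concern.** The freely allowed co-treatment acts on the disease that the GELP score measures. Section 10.1 cites an earlier randomised trial in which photodynamic therapy and topical corticosteroid had comparable effects, with mean GELP falling from 11 to 7. The same 4 points are then assumed as the difference between apremilast and a placebo arm with open access to steroid.

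The diary measure has a ceiling. Section 1.2 says potent topical steroid is first-line and usually needed for life, so daily use at entry is plausible, although the protocol gives no distribution. For a patient at 7 days per week, going from one application a day to two, adding the vagina to the vulva or changing product leaves the record unchanged. GELP scores the two sites separately, so the site treated is relevant. Non-steroid genital topicals that are not immunomodulating are not barred, and section 5.4 does not ask for them to be recorded.

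At stake is how a null or small difference can be read. If placebo patients compensate with more steroid in ways that days per week does not capture, the SAP cannot recover this, because the data will not exist.

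The second matter is separate. A baseline value that may predict the outcome is collected and then left out of the primary model, in an unstratified trial of 42 patients.

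**Working it through.** **1. The plan's own sample size.** Inputs from section 10.1: difference 4, SDs 4.5 and 4.2, 5% level, 80% power, independent samples t-test. The test is taken as two-sided because section 10.5.1 states the alternative as a difference.

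- Pooled SD = sqrt((4.5² + 4.2²)/2) = 4.35.
- Noncentrality at 20 per group = 4 / (4.35 × sqrt(2/20)) = 2.91, with 38 degrees of freedom.
- Power from the noncentral t: 78.7% at 19, 80.8% at 20 and 82.8% at 21 per group.

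The stated 20 per group is reproduced.

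**2. What dilution would do.** The documents do not say how much extra steroid placebo patients would use or what it would achieve, so the reduction is an assumption, shown as a range. The calculation is the same with the difference reduced.

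| Assumed extra GELP fall on placebo | Remaining difference | Power at 20 per group | Per group for 80% |
|---|---|---|---|
| 0 | 4.0 | 81% | 20 |
| 0.5 | 3.5 | 70% | 26 |
| 1.0 | 3.0 | 57% | 35 |
| 1.5 | 2.5 | 43% | 49 |
| 2.0 | 2.0 | 29% | 76 |

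Only the part of such use that leaves days per week unchanged would be hidden. The rest would show in the secondary endpoint.

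**3. Chance imbalance at baseline.** Assume half the patients use steroid daily at entry.

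- SD of the difference in proportions at 21 per arm = sqrt(0.25 × 2/21) = 0.154; 95% range ±1.96 × 0.154 = ±0.30.
- If daily users differ by 1 to 4 GELP points at week 24 (assumption), a 1-SD imbalance moves an unadjusted comparison by 0.154 × 1 = 0.15 to 0.154 × 4 = 0.62 points.
- The standard error of that comparison is 4.35 × sqrt(2/21) = 1.34, so the shift is 0.11 to 0.46 standard errors.

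The confidence interval already allows for this random error. Adjustment would remove part of it.

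**4. Gain from the covariate.** Residual SD = 4.35 × sqrt(1 − R2), where R2 is the assumed share of residual variance explained by week-0 steroid days. The calculation uses 20 per group, 36 degrees of freedom and a difference of 4.

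| Assumed partial R2 | Residual SD | Power |
|---|---|---|
| none (t-test) | 4.35 | 81% |
| 5% | 4.24 | 83% |
| 10% | 4.13 | 85% |
| 20% | 3.89 | 89% |

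This takes no credit for baseline GELP. If baseline GELP correlates 0.5 with the week-24 score (assumption), power is already 90% and the same range of R2 raises it to 92-95%.

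If the difference has been diluted to 2.5, adding the covariate gives only 44-51% for R2 of 5-20%, without credit for baseline GELP. The covariate does not undo use that changes after randomisation.

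**The case against.** The case on the other side is substantial.

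- **Steroid days are seen.** A reader might infer that co-treatment can differ between arms unnoticed. That is too strong. Steroid days are a weekly secondary endpoint with a 4-week baseline, and section 10.5.6 assigns intercurrent-event handling to the SAP. Only applications per day, site, product and other genital topicals are missing from the stated measure.
- **Other recording rules exist.** Section 9.2 asks medical records to describe treatments given and changes to them, and section 8.5 asks for treatments given for an adverse event. This stands in part: neither defines a weekly variable that can be compared by arm.
- **Dilution is part of the design and conservative.** This stands. Section 1.4 declares an add-on comparison, and extra steroid on placebo pulls the difference towards zero, so it does not favour a false superiority claim. The remaining difficulty is how to explain a null result.
- **The 4-point fall is not the effect of extra applications.** This stands. It is a before-after change, and section 1.2 gives the corticosteroid regimen as daily application over six weeks. It shows that steroid may matter, not how much escalation in an existing user would add.
- **Leaving out the covariate causes no bias.** This stands. It also means that adding it cannot answer worries about use driven by allocation.
- **Barrier creams.** Section 1.4 advises "use of topical treatments such as moisturizing and barrier creams at initiation of treatment to reduce this", and one might suspect an effect of their use on the primary result. The protocol places the irritation in the first weeks and says the gastrointestinal reactions usually resolve within 4 weeks. It offers no route to a week-24 effect.

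**Conclusion.** The point holds in a limited form, as two inexpensive improvements worth making.

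First, the steroid measure cannot show escalation in a patient already at 7 days per week, and section 5.4 has no recording rule for non-steroid genital topicals. Any resulting dilution is conservative, but a null result could not be told apart from compensation by placebo patients within that ceiling. The size is unknown. An extra placebo fall of 0.5 to 2 points would take power at 20 per group from 81% to between 70% and 29%, and those inputs are assumptions.

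Second, week-0 steroid days are available and unused in the primary model. The loss is one of precision: about 2 to 8 percentage points of power at an assumed partial R2 of 5-20%, and less if baseline GELP is itself strongly prognostic.

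The documents do not support reading this as a biased primary comparison, as wholly unobserved co-treatment, or as a problem of post-randomisation use that a baseline covariate would cure.

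**What to change.** 1. In section 10.5.3, prespecify week-0 steroid days per week as a second covariate beside baseline GELP. The value is already collected, and section 10.4 allows changes to the analysis plan until database lock. The cost is one degree of freedom. The gain depends on prognostic strength that the documents do not give.

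2. Keep days per week as the secondary endpoint. Add to the weekly diary the number of steroid applications, the product and the site (vulva or vagina). Extend the recording rule in section 5.4 from systemic medication to include all topical products used in the genital area. The cost is a few fields and slightly more patient burden. The protocol gives 24.09.2019 as the date of first enrolment, so the new data will be missing for patients already treated, and a comparison by arm should state whom it covers. Permitted care does not change.
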